### Hypotheses and objectives

In view of the uncertainty regarding the risk/benefit ratio of supplemental parenteral nutrition, we aim to investigate which of two management options (initiation of supplemental parenteral nutrition or no introduction of parenteral nutrition) proves to be superior in terms of health-related quality of life without a significant decrease in survival, in the palliative phase of cancer.

The primary objective of the ALIM-K study is to evaluate the clinical benefit in terms of health-related quality of life, as evaluated at 2 months (or at treatment discontinuation for patients who discontinue treatment allocation before 2 months), by using the European Organisation for Research and Treatment of Cancer (EORTC) Quality of Life Questionnaire Core 15 Palliative (QLQ-C15-PAL), and in particular, the physical function, global health, and fatigue subscales [13], of the initiation of supplemental parenteral nutrition as compared with no parenteral nutrition, in malnourished cancer patients at the palliative stage who have a functional digestive tract, and in the absence of any curative therapy.

Secondary objectives are to compare the effects of both types of nutrition on overall survival and nutritional parameters.

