#### Sample size and recruitment

In a bilateral situation, a *P* value of <0.0166 will be considered clinically and statistically significant after Bonferroni adjustment for multiple testing, to ensure an overall bilateral alpha risk of 5%. To detect the minimal clinically significant difference (at least 10 points, with a standard deviation of 11 points), with a bilateral alpha risk of 0.0166 and a power of 80%, 54 patients per group are required. Interim analysis to evaluate the primary hypothesis is planned when half the patients have been included and have at least 2 months of follow-up. This interim analysis will be performed according to the rules established by O’Brien and Fleming (Alpha Spending Function with bounds calculated by O’Brien’s method) [24].

The calculation of the sample size takes into account the specificity of the randomization by the Zelen design, and the primary end point of quality of life measured with a multidomain questionnaire: Two groups of equal size, constituted by random assignment; one group will receive standard therapy, and the other group will receive the experimental therapy, or standard therapy if the patients refuses to consent to experimental therapy. The heterogeneity of the intervention group will increase the variance of the difference (Δ_z_) between groups for the primary end point, as compared with classic randomization (Δ_c_), albeit without introducing a measurement bias. The increase in variance will increase with the percentage (Φ) of subjects who receive standard treatment in the intervention group, with [25].

In these conditions, the number of subjects must be multiplied by (1/(1 - Φ)^2^). For the ALIM-K study, we estimate that the percentage (Φ) of subjects who receive standard treatment in the intervention group will be low (estimated at around 10% by experts). Quality of life, as measured by the questionnaire, will yield a score for each domain. To take into account the multiplicity of comparisons, the Bonferroni correction will be applied to the alpha risk.A variation in quality-of-life score of at least 10 points (on a scale of 0 to 100) will be considered as clinically significant.

At an alpha risk of 0.0166, power of 80%, and a percentage Φ of 10%, the number of subjects required to detect a difference of at least 10 points (±11) in quality-of-life score is at least 70 per group (54 × 1.25), or 140 patients in total.

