#### Primary objective

A treatment group will be considered as superior to the other if at least one of the three domains of the primary end point (physical function, overall health status/quality of life, or fatigue) of the QLQ-C15-PAL questionnaire is clinically and statistically significantly better, without any clinically and statistically significant deterioration in at least one of the other two domains.

Comparison of the three domains of the QLQ-C15-PAL questionnaire (between the parenteral nutrition and oral feeding groups) will be performed on an intention-to-treat basis for all patients randomized and included, by using ANOVA on scores at 2 months. Analyses will be adjusted for the presence (or not) of palliative chemotherapy. The variation in the score for each domain between inclusion (day 1) and day 60 will be compared with ANOVA, taking into account stratification variables and potential confounding factors, such as center, type of cancer, and patient characteristics.

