#### Change in quality of life over time

Quality-of-life scores will be generated according to algorithms described in the EORTC scoring manual. The mechanism of missing scores will be studied and classified according to the methods of Diggle [26] and Rubin [27] (that is, MCAR (Missing Completely At Random), MAR (Missing At Random), and MNAR (Missing Not At Random). The mechanism of missing data will be determined by comparing patients with no missing scores with those with at least one missing score at baseline, according to baseline characteristics of patients. If required, more detailed patterns will be defined. If missing data are MNAR, multiple imputations may be performed. Otherwise, simple imputation by the mean will be retained.

The time to quality-of-life score deterioration (TTD) will be defined as a modality of longitudinal quality-of-life analysis and will be defined as the time from inclusion in the study to a first deterioration, with a minimum clinically significant difference of at least 5 points as compared with the baseline score, or death of any cause, whichever occurs first [28, 29]. Although three domains of the EORTC QLQ-C15-PAL are being targeted for the primary end point, scores from all domains of the questionnaire will be studied as secondary analyses. The TTD curves will be calculated by using the Kaplan-Meier method and described, by using median and 95% confidence interval (CI). TTD curves will be compared according to treatment group by using the log-rank test and univariate Hazard Ratio with 95% CI. A multivariate Cox regression model will then be performed to investigate potential prognostic factors of TTD. All variables collected at baseline will be tested by univariate analysis. Variables with a *P* value ≤0.20 by univariate analysis will be eligible for inclusion in the multivariate Cox analysis.

Mixed-model analyses of variance for repeated measures will also be performed to test a time effect, a treatment effect, and an interaction between time and treatment. If missing data are not completely at random, a pattern-mixture model will be used.

Analysis of the secondary end points will focus first on comparison of overall survival. Overall survival is defined as the time from study registration to death of any cause. Patients who are lost to follow-up will be counted at the date of their last follow-up.

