For all time-to-event end points, the 95% CI of the median survival will be calculated with the Brookmeyer and Crowley method [30]. The two treatment arms will be compared with the log-rank test.

Hazard ratios with 95% CI will be estimated by using Cox’s univariate proportional hazards model. Follow-up will be estimated by using reverse Kaplan estimation.

A multivariate Cox regression model will be performed to investigate potential prognostic factors. All variables collected at baseline will be tested in univariate analysis. Variables with an univariate *P* value ≤0.20 will be eligible for multivariate Cox analysis. A bootstrap procedure will be used to check internal validation of the model. The discriminatory capacity of the model will be assessed with Harrell C statistic. Reclassification ability will be examined with Net Reclassification Improvement (NRI) [31] and Integrated Discrimination Improvement (IDI) [32].

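### The rule for declaring a feeding group superior leaves out the survival condition that the trial's own hypothesis contains

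*Protocol article*

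**What the plan says.** The section Hypotheses and objectives sets out to learn which of the two options "proves to be superior in terms of health-related quality of life without a significant decrease in survival". The labelled primary objective that follows concerns quality of life only, and survival comes next: "Secondary objectives are to compare the effects of both types of nutrition on overall survival and nutritional parameters".

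Under Statistical analysis, Primary objective, the decision rule reads "A treatment group will be considered as superior to the other if at least one of the three domains of the primary end point" shows a gain that is both clinically relevant and statistically significant, "without any clinically and statistically significant deterioration in at least one of the other two domains". That is the only safeguard in the rule, and it concerns quality of life.

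Survival is handled under Change in quality of life over time: "Analysis of the secondary end points will focus first on comparison of overall survival", and "The two treatment arms will be compared with the log-rank test". A Cox hazard ratio with 95% confidence interval is also planned.

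For the interim look, Sample size and recruitment says: "Interim analysis to evaluate the primary hypothesis is planned when half the patients have been included and have at least 2 months of follow-up". It adds: "This interim analysis will be performed according to the rules established by O’Brien and Fleming". It names no survival condition and does not say what action follows if the bound is crossed.

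**The concern.** The protocol uses the word superior in two places with two meanings. In the hypothesis it has two parts: better quality of life, and no significant loss of survival. In the rule that will be applied to the data it has only the first part. The two meanings give opposite verdicts in the case that the survival clause exists to catch.

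The protocol's Background treats that case as open. It mentions a view that artificial nutrition might speed tumour growth, lists serious complications of parenteral nutrition, and cites a randomized trial in which parenteral nutrition prolonged survival. The rule is also symmetric: oral feeding could be declared superior on quality of life with significantly shorter survival. At stake is whether the headline claim answers the question that the trial poses.

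**Working it through.** **1. The two definitions side by side**

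| Result for an arm | Hypotheses and objectives | Primary objective (rule) |
|---|---|---|
| Quality-of-life criteria met; survival not shorter | superior | superior |
| Quality-of-life criteria met; survival shorter, not significantly | superior | superior |
| Quality-of-life criteria met; survival significantly shorter | not superior | superior |
| Quality-of-life criteria not met | not superior | not superior |

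They disagree only in the third row. This needs no arithmetic. The rest shows how much it could matter.

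**2. The plan's sample size**

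The plan gives no figure for the survival condition. The check borrows the sample size: 10 points, SD 11, two-sided alpha 0.0166, 80% power, stated as 54 per group and raised to 70 per group (140 in total) for 10% refusal. The usual formula gives 2 × (2.395 + 0.842)² × 11² / 10² = 25.4, so 26 per group (27 with the t distribution). The stated 54 matches the two-group total, or an SD of 16. The present point does not depend on this, and I take the stated 70 per group as the size of the trial.

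**3. How strongly a survival clause would act**

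Inputs: 1:1 allocation (Trial design). Assumed: a two-sided 5% level and a true hazard ratio (HR) for death of 1.5, since the protocol gives neither. With D deaths, power = Φ(ln HR × √D / 2 − 1.96).

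- D = 40: Φ(0.405 × 3.16 − 1.96) = 0.25
- D = 60: Φ(0.405 × 3.87 − 1.96) = 0.35
- D = 140: Φ(0.405 × 5.92 − 1.96) = 0.67

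For 80% power, D = 4 × (1.96 + 0.842)² / 0.405² ≈ 191, more than the 140 patients. The same section also plans 16 patients in each of 10 centres, or 160. With 160 deaths the power is Φ(0.405 × 6.32 − 1.96) = 0.73, and 191 is still out of reach. With 140 deaths, the smallest observed hazard ratio that reaches significance is exp(1.96 × 2 / √140) = 1.39. A clause based on non-significance therefore protects weakly, although the rule as written gives no protection.

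**4. The interim look**

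- Bound at half the information: 2.395 / √0.5 = 3.39 (3.40 when the two-look bounds are solved exactly; p = 0.0007).
- Standard error with 35 evaluable patients per group: 11 × √(2/35) = 2.63. The bound corresponds to 3.39 × 2.63 = 8.9 observed points.
- The rule also asks for clinical relevance, taken here as an observed 10 points. That exceeds 8.9, so it governs.
- Chance that one given domain meets both criteria: true 10 points, Φ(0) = 50%; true 9 points (10 × 0.90, diluted by refusal), Φ((9 − 10) / 2.63) = 35%. The bound alone would give 66% and 51%.
- With SD 16 the standard error is 3.82, the bound is about 13 points and governs, and the chances are 22% and 15%.

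Deaths at that look are not given. Assume 70 patients entering evenly over 15 months (half of the planned 30), 2 further months, and exponential survival with a median of 3 to 9 months. That gives 58 to 34 deaths, and a log-rank power of 34% to 22% for a hazard ratio of 1.5.

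The 35 evaluable per group is favourable. With a 3-month median, 63% would be alive at 2 months, about 22 per group, and the chance for a true 10 points falls to about 35%, unless scores at treatment discontinuation fill the gap.

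**The case against.** The labelled primary objective is quality of life alone, survival is a declared secondary objective, and the rule agrees with both. Survival is the first secondary comparison, by intention to treat, so a loss of survival would be reported. A formal analysis plan is still to come. All of this stands, and it means that harm would not be hidden. It does not remove the mismatch. The hypothesis uses the same word with a further condition, and the article writes the rule out in full, including a safeguard, so this is not a detail left for later.

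A reader might infer more: that the trial can stop at half size, freeze the survival comparison, and declare superior an arm that shortens survival. The document does not support that reading.

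- It never says that the trial stops at the interim look. Stopping is only suggested by the use of O'Brien-Fleming bounds.
- It says that the look evaluates the primary hypothesis, which may be read back to the sentence with the survival condition.
- Table 2 and the visit schedule already plan follow-up until death, and nothing ends it at the interim.
- The hypothesis bars only a significant decrease. On the figures above, an arm with a true hazard ratio of 1.5 would still pass it in about 65 to 75% of trials with 40 to 60 deaths.

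**Conclusion.** The point holds as a mismatch between the stated hypothesis and the stated decision rule. Followed exactly, the rule can declare superior an arm that fails the trial's own hypothesis. That conclusion rests on the text alone.

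Its size rests on assumptions. The hazard ratio of 1.5, the 5% level and the death counts are not in the protocol, and the joint chance of better quality of life with worse survival has not been estimated. Early stopping is a possible consequence only. The 50% and 35% are for one given domain, on the plan's SD with 35 evaluable patients per group, and leave out the safeguard on the other domains. The point merits a correction because the headline claim depends on the rule and the change is small.

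**What to change.** 1. In Primary objective, add the survival condition of the hypothesis to the rule. A group is superior only if the quality-of-life criteria are met and its survival is not significantly shorter. Use the log-rank test and Cox hazard ratio already planned, in all randomized patients, and state the significance level.
2. Report the hazard ratio and its 95% confidence interval beside any superiority claim, because non-significance alone is weak evidence of no harm at this size.
3. In Sample size and recruitment, state that the primary hypothesis tested at the interim look includes the same condition, that crossing the quality-of-life bound alone does not support a superiority claim, and that the planned follow-up to death continues.

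The cost is wording in two sections and one survival comparison at a look that is already planned. The sample size does not change. Superiority becomes slightly harder to declare and may be declared later.

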#### Intervention in each group

Two groups will be constituted by random allocation. In the intervention group (“parenteral nutrition” group), parenteral nutrition will be initiated, whereas in the control group (“oral feeding” group), nutrition will be exclusively by the oral route, without parenteral nutrition.

At inclusion, patients in both groups will be evaluated by a dietitian with the aim of allowing all patients, regardless of the treatment group to which they are allocated, to pursue oral feeding where possible. Initial evaluation will record the following data: ➢ Anthropometric data (weight, ideal weight, height, BMI)➢ Dietetic advice given (previously or during evaluation) regarding uncomfortable symptoms➢ Estimation of theoretic energy requirements in kcal [18] adjusted by a correction factor for the cancer➢ Estimation of theoretic protein requirements (1.2 to 1.5 g of protein per kilogram (kg) per day) [19]➢ Quantitative estimation of daily intake in terms of calories and protein (over 24 hours, as reported by the patient)➢ Visual or verbal analog scale of calorie and protein intake (measured on a scale from 0 to 10)➢ Number of eating intakes per day➢ Oral nutritive supplements: type, dose, and protein-energy content.

The dietitian’s main tasks will be as follows: ➢ To provide appropriate dietetic advice aimed at spacing out and enriching food intake➢ To provide specific advice on the management of symptoms related to food intake, such as anorexia, dry mouth, early satiety, dysgeusia, nausea, vomiting, chewing/swallowing disorders, transit disorders➢ To propose, where necessary, prescription of oral nutritional supplements.

In the “oral feeding” group, patients will pursue exclusive oral feeding as usual, tailored to the patient’s needs by a dietitian or nutritionist, according to local practice in each center.

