#### Criteria for discontinuing or modifying allocated interventions

Parenteral nutrition may be discontinued at any time by the investigator or by the patient. Discontinuation is mandatory in case of uncontrolled hydroelectrolyte imbalance, insulin-dependent diabetes with persistent fasting glycemia >2 g/L, triglycerides >3 m*M*, or intra- or extraluminal infection.

If the treating physician of a patient allocated to the “oral feeding” group decides, during follow-up, to initiate enteral or parenteral nutrition (irrespective of the reason, including at the request of the patients or their close relatives), follow-up within the ALIM-K study will continue according to the modalities stipulated for the group to which the patient was initially randomized.

In case of serious adverse events or effects leading to discontinuation of the type of feeding intended for the group to which the patient was initially allocated, the patient will be followed up according to the modalities stipulated for that group, because follow-up corresponds to standard recommended practices.

The investigator may decide at any time to change the patient’s management, whether for reasons related to safety, behavior, or administrative requirements, or for any other reason the investigator judges relevant.

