#### Outcomes

**Primary outcome** The primary end point is health-related quality of life specific to the palliative phase of cancer, evaluated at 2 months (or at treatment discontinuation for patients who discontinue treatment allocation before 2 months), by using the European Organisation for Research and Treatment of Cancer (EORTC) Quality of Life Questionnaire Core 15 Palliative (QLQ-C15-PAL), in particular, the physical function, global health, and fatigue subscales [13].

The QLQ-C15-PAL will be proposed to the patient at inclusion in the study, and at every follow-up visit until death. If necessary, help is available for patients to complete the questionnaire (reading out the questions, explaining the different response options, taking any notes). The QLQ-C15-PAL is the short version of the QLQ-C30 adapted for patients in palliative care [13]. The 15 items are divided into two functional subscales (physical function, three items; and emotional function, two items); two symptom subscales (fatigue, two items; and pain, two items); five single items (dyspnea, appetite loss, sleeping disorders, constipation, and nausea/vomiting), and one item evaluating global health status/quality of life. Linear transformation of the item responses yields a score for each subscale (or single items) ranging from 0 to 100. A higher score corresponds to a higher level of global quality of life and functional aspects, and a greater level of symptoms on the symptom scale. The subscales physical function, global health status/quality of life, and fatigue will be evaluated for the primary end point. The minimum clinically significant difference is fixed at 10 points [21].

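### The endpoint definition (2 months or earlier discontinuation) and the primary ANOVA (2-month scores) do not match, and neither says how a death before day 60 enters; early or pre-death scores may therefore count unequally in the two arms

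*Protocol article*

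**What the plan says.** The endpoint and its analysis are described in different terms.

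- **Endpoint** (Outcomes, primary outcome; repeated under Hypotheses and objectives). Quality of life is "evaluated at 2 months (or at treatment discontinuation for patients who discontinue treatment allocation before 2 months". The clause is not limited to one arm.
- **Analysis** (Statistical analysis, Primary objective). The three domains are compared "on an intention-to-treat basis for all patients randomized and included", "by using ANOVA on scores at 2 months". A second analysis reads: "The variation in the score for each domain between inclusion (day 1) and day 60 will be compared with ANOVA". The discontinuation clause is not repeated, and death is not mentioned.
- **Leaving the allocation** (Criteria for discontinuing or modifying allocated interventions). "Parenteral nutrition may be discontinued at any time by the investigator or by the patient", and some conditions make stopping mandatory. For controls the section foresees that the treating physician "decides, during follow-up, to initiate enteral or parenteral nutrition". It also foresees that a serious adverse event ends the allocated type of feeding in either arm. Follow-up then continues in the randomized group.
- **Control arm** (Intervention in each group). "patients will pursue exclusive oral feeding as usual".
- **Missing scores** (Change in quality of life over time). Multiple imputation may be used if scores are missing not at random. "Otherwise, simple imputation by the mean will be retained". Death is not mentioned.
- **Death in a quality-of-life analysis.** It appears only as an event in the secondary time to deterioration.

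**The concern.** Patients are malnourished, at the palliative stage, and enter on an estimated life expectancy above 2 months. The endpoint falls at 2 months, so some deaths before it are to be expected.

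The time at which the endpoint is read depends on an event after randomization that does not mean the same thing in both arms. Parenteral nutrition is a discrete treatment with a clear stopping point, and that point may come shortly before death. Usual oral feeding has no natural counterpart. Under the endpoint definition, some patients in the parenteral-nutrition arm who die early could supply a score at stopping, while most controls who die early may supply none. Patients who stop parenteral nutrition and live on would also be scored earlier than controls. Under the analysis sentence, all patients dead by day 60 drop out of both arms, although the comparison is meant to include everyone randomized. Under the imputation default, a dead patient could be given an average score.

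These are three different primary comparisons, and the text allows each of them. In none of them does death count as a poor outcome in both arms alike. At stake is whether the 2-month difference still compares like with like, in a trial that claims superiority on a 10-point difference in a single domain.

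**Working it through.** **Side by side.** The endpoint definition admits a score taken before 2 months; the ANOVA sentences name 2 months and day 60 only. Read alone, the ANOVA sentence creates no asymmetry, because it leaves out early deaths in both arms. The asymmetry appears once the endpoint's discontinuation clause is carried into the ANOVA.

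**Figures in the article.** None exists for deaths by day 60, for discontinuation, or for the score gap before death, so there is no stated figure to reproduce. Three figures are taken from Sample size and recruitment as they stand: 70 per group, SD 11 and two-sided alpha 0.0166.

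**Assumed inputs.** Share dying before day 60, d, equal in both arms: 20–30%. Deficit of pre-death scores against survivors, gap: 10–20 points. Share of deaths with a usable discontinuation score: f = 25–100% in the parenteral-nutrition arm, g in the control arm. No true treatment effect.

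**Formula.** The weight of pre-death scores in an arm's mean is d·f/(1 − d + d·f), and likewise with g for controls.

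Shift = −gap × [d·f/(1 − d + d·f) − d·g/(1 − d + d·g)]

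**No control death scored (g = 0).** Entries are points against parenteral nutrition.

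| d | gap | f = 0.25 | f = 0.5 | f = 1 |
|---|---|---|---|---|
| 20% | 10 | 0.59 | 1.11 | 2.00 |
| 20% | 20 | 1.18 | 2.22 | 4.00 |
| 30% | 10 | 0.97 | 1.76 | 3.00 |
| 30% | 20 | 1.94 | 3.53 | 6.00 |

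Smallest: 10 × 0.05/0.85 = 0.59. Largest: 20 × 0.30/1.00 = 6.00. At d = 10% the range is 0.27 to 2.00.

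**Some control deaths scored (d = 20%, gap = 20, f = 0.5).**

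- g = 0: 20 × 0.10/0.90 = 2.22 points.
- g = 0.25: 20 × (0.10/0.90 − 0.05/0.85) = 20 × (0.1111 − 0.0588) = 1.05 points.
- g = 0.5: zero.

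**False rejection in those three cases.** A z-test per domain was used. The number scored is 70 × (1 − d + d·f) in the parenteral-nutrition arm, with g for controls. Each arm's variance is 11² + gap² × w(1 − w), where w is the weight above. For g = 0 the numbers scored are 63 and 56, the standard error is 2.17, and the two-sided rejection rate is 8.5% against a nominal 1.66%. For g = 0.25 it is 2.9%. For g = 0.5 it is 1.66%.

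**Direction.** The formula takes the early scores to be lower than survivors' scores. If a stopping score is taken before decline sets in, the gap changes sign and the shift favours parenteral nutrition. The same holds for patients who stop early, are scored then, and would have declined by day 60.

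**Dropping deaths from both arms.** This is not neutral if mortality differs. The assumptions are a logistic death model with log-odds 1 per SD of score, 20% deaths in one arm and 30–40% in the other. Survivor means then differ by about 0.9 to 3.2 points over SD 11 to 20, with no effect on any patient's score. With the article's SD of 11 the range is 0.9 to about 1.7.

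**The case against.** A reader might infer that a dying control contributes nothing while every dying parenteral-nutrition patient is scored, so that the comparison is certainly biased against parenteral nutrition by 2 to 6 points. The article does not support this.

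- The discontinuation clause is worded for both arms, and controls can leave their allocation.
- Controls complete questionnaires at visits at least monthly before day 60 and on until death, so pre-death control scores exist, although no text makes the last one the endpoint.
- A patient who dies while still on parenteral nutrition has no discontinuation score. The schedule lists no separate discontinuation visit. The roughly 10% expected to refuse parenteral nutrition stay on oral feeding and resemble controls.
- Two to 6 points is the extreme case, with every parenteral-nutrition death scored and no control death scored.
- Mean imputation sits under the longitudinal analysis, and the primary analysis does not invoke it.

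There is also partial cover elsewhere. Time to deterioration counts death alike in both arms for all domains, overall survival is the first secondary comparison, a pattern-mixture model is foreseen for the longitudinal analysis, and a formal analysis plan is promised before database lock.

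All of this limits the wording and the size. It does not remove the mismatch. The endpoint definition is fixed in the article itself, so this is more than detail left to a later plan, and the safeguards named are secondary analyses that do not say what the primary comparison estimates.

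**Conclusion.** The point holds in a limited form. The endpoint definition and the primary analysis do not agree on when quality of life is read, and neither states how a death before day 60 enters. Because parenteral nutrition can be stopped at any time and usual oral feeding seldom has a stopping point, early or pre-death scores will probably enter more often from the parenteral-nutrition arm. The 2-month difference may then be biased, in either direction.

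The size cannot be fixed from the article. Under the assumed ranges, with no control death scored, it is about 0.6 to 6 points, and it falls to zero as the scored shares become equal. The upper end is a bound, not an expectation. Even mid-range values matter for a test at 0.0166, as the 8.5% example shows. This should be settled before the planned interim analysis of the primary hypothesis.

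**What to change.** Reconcile the endpoint definition (Hypotheses and objectives; Outcomes) with the Primary objective section as follows.

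1. Use the day-60 assessment for every patient alive then, in both arms, whether or not the allocation was discontinued. Questionnaires are already collected until death. This also removes unequal timing among survivors, which dropping stopping scores for the dead alone would leave in place.
2. State that neither a discontinuation score nor mean imputation stands in for a patient who died before day 60.
3. Describe the ANOVA as a comparison among patients alive at day 60, since it cannot speak for all those randomized.
4. Pre-specify, for each of the three primary domains, a companion rank analysis stratified by center in which death before day 60 ranks below every observed score. Report it beside the ANOVA and consider it when interpreting any superiority claim. An automatic veto based on its direction is not needed and would be hard to define across three domains.

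The cost is a little more analysis and no new data. The drawback is that the rank result is not expressed in questionnaire points.
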